### Timeline

Figure 2 shows the study timeline. Inclusion into this trial started in September 2014. We plan to use 2 years for inclusion of at least 600 study participants and to finish the follow-up data collection during 2017. Data preparation, statistical analyses, manuscript preparation and publication in peer-reviewed scientific journals are planned for 2017 to 2019.

### Ethical considerations

The trial raises ethical issues related to risks of the treatments, the integrity of the study participants, how the collected information will be protected and how research results will be reported. The study collects data from people with symptoms in the neck. The study is based on informed consent, and the information to study subjects clearly states that the study is voluntary and that participants may terminated participation at any time. When collected data are analyzed, personal numbers will be replaced with serial numbers. All collected data will only be used for the purpose of this research, and all in the research group has the ethical principle of confidentiality. The results from the trial will only be presented in tables and figures where no individuals can be identified.

**Fig. 1 Fig1:**
[figure not shown]
Study procedures

**Fig. 2 Fig2:**
[figure not shown]
Study timeline

We will process data in accordance with federal guidelines and laws PuL (1998:2004). In addition, we will work actively and continuously to deal with ethical issues that arise during the study. Written informed consent will be obtained from all study subjects.

The treatments are considered safe with very low risk of severe adverse events. We estimate that the benefits of the study will be far greater than any possible risk. The trial has been approved by the Regional Ethics Committee in Stockholm 2014/755-31/3 and is registered at the database Current Controlled Trials (ISRCTN01453590).

## Discussion

Neck pain is one of the most challenging public health issues worldwide. Given its prevalence, the need to assess effective approaches for neck disorders is of prime importance. Although management of non-specific neck pain disorders often includes massage therapy as well as exercise therapy intervention or promotion, little is known about the effectiveness, side effects and cost-effectiveness of such therapies. Scientific evidence supports such therapies for the treatment of low back pain, but their effectiveness for neck pain has not been established. This RCT aims to increase the knowledge on the efficiency, cost and safety of these commonly used treatments for neck pain.

### Strengths

The strengths of this trial includes rigorous randomization procedure, long-term follow-up, the use of standardized outcome measures and a large study population enabling subgroup analyses of the effect of the interventions. The weekly measure of neck pain intensity and neck pain-related disability enables not only a careful follow-up of the effect of the interventions, but also a detailed description of the course of neck pain during a 1-year period, which is an important knowledge for planning of healthcare and secondary prevention strategies. Given the study design, the measurement of the cost-effectiveness of such therapies will be possible. In order to be able to discuss the balance between efficacy and harm, adverse events will be measured (duration and severity) in direct conjunction to the interventions in a standardized way, as described in previous studies of our group on manual therapy [24, 26, 27].

### Limitations

One of the major methodological difficulties inherent to studies evaluating physical interventions is blinding of therapists and study participants. The nature of the interventions makes it impossible to blind the care provider and difficult to blind the study participant.

Unmasking will be performed by the care provider after the physical examination, the second-step exclusions and the data collection with baseline questionnaires, so the study administrator, the therapist and the study participant all will be blind to the group assignment until after all baseline data is collected. We will measure study participant’s previous experience of the interventions, expectation of recovery and expectation of the importance of the allocated therapy for the recovery (just after the unmasking and before the intervention starts). In an attempt to minimize bias from potential differences in expectations of recovery between the four groups will test the potential confounding effects of these factors in the statistical analyses.

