## Methods/Design

### Study design

The study design is a randomized controlled trial. At least 600 study participants with long-lasting or subacute neck pain will be randomized to one of four treatment arms. To be able to discuss the balance between effectiveness and harm in the treatment arms, adverse events will be monitored with a questionnaire after each visit [24].

A blinded trial is not possible in this case because of the character of the interventions. Attempting to compensate for the lack of blinding, we measure study participant’s previous experiences of the interventions. Furthermore, we ask them about their expectations of recovery before randomization allocation and about their expectations of treatment effect right after finding out the treatment to which they have been allocated.

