### Statistical analyses

The comparison of the effect between the groups statistical analyses will be performed using an “*intention to treat”* principle aimed at analyzing participants in the group to which they were originally assigned and to keep the dropouts in the assigned group no matter what the reason [57]. To estimate the impact of missing responses, sensitivity analysis for the primary outcomes will be performed using multiple imputation [58]. Changes in mean scores at follow-up compared with baseline, and differences in changes between groups will be calculated by unpaired t-test. To compare the groups regarding the dichotomized outcomes, relative risks (RR) and risk differences (RD), together with corresponding 95 % confidence intervals (CI), will be calculated. Baseline factors that differ between the treatment groups will be considered with regard to their potential confounding effect by means of Mantel Haenszel’s method [59]. If adjustment is needed, the Cox proportional Hazard model will be used.

Generalized estimating equations (GEE) will be performed to analyze the effect on the primary outcome (pain and disability) over the total follow-up time, including the automated text messages (SMSes). The GEE method extends standard regression analysis, taking into account the covariance between repeated measurements of pain and disability [60, 61].

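### Expectation of the allocated therapy, asked after unmasking, is listed for testing as a confounder, although allocation can cause it and the analysis section admits only baseline factors

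*Protocol article*

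**What the plan says.** Two different expectations are collected. Under Study design, the investigators write that "we ask them about their expectations of recovery before randomization allocation", and then that they ask "about their expectations of treatment effect right after finding out the treatment to which they have been allocated". The reason given is the absence of blinding: "A blinded trial is not possible in this case because of the character of the interventions".

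The Limitations section repeats the timing. It names three items: whether participants have had the treatments before, how far they expect to recover, and, as the third, "expectation of the importance of the allocated therapy for the recovery (just after the unmasking and before the intervention starts". Its next sentence gives the purpose, which is to limit bias from expectations that differ across the four groups, and says the trial "will test the potential confounding effects of these factors in the statistical analyses".

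The Statistical analyses section sets the comparison principle as intention to treat, "aimed at analyzing participants in the group to which they were originally assigned". On confounding it says: "Baseline factors that differ between the treatment groups will be considered with regard to their potential confounding effect by means of Mantel Haenszel’s method". It continues: "If adjustment is needed, the Cox proportional Hazard model will be used".

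Table 4 places previous experience in Baseline A and expectation of recovery in Baseline B. Expectation of the allocated therapy is in neither. Both Randomization procedure and Limitations say that everyone involved stays blind to the assignment until all baseline data have been collected.

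**The concern.** Confounding of a treatment comparison needs a variable that influences the outcome and is associated with treatment without being a consequence of it. Previous experience and Baseline B expectation of recovery are fixed before the arm is known, so they can differ between arms only by chance and are legitimate covariates. Expectation of the allocated therapy is different. The participant answers after learning whether the arm is massage, exercise, both or advice, so the answer may itself be an effect of allocation.

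Adjusting for such a variable does two things. It takes out whatever part of the treatment effect runs through expectation. It also opens a path through any unmeasured cause shared by expectation and outcome (a person's general optimism, for example), which randomisation had closed. Pain and disability are self-reported, so both routes are plausible.

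An empirical screen makes this worse. A search for factors that differ between arms would tend to select this variable if allocation changes it, and those are the cases in which adjustment does harm. Nor does adjustment undo the lack of blinding: isolating an effect free of expectation would require that no unmeasured common cause of expectation and outcome exists.

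**Working it through.** **1. Is the variable post-randomisation?** Study design and Limitations agree that it is asked after the assignment is revealed. Yes.

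**2. Is it in the set to be tested?** The plural reference in Limitations follows a three-item list that includes it, and nothing removes it.

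**3. Does the analysis section allow it?** That section restricts the screen to baseline factors. Baseline data are complete before unmasking (Randomization procedure, Limitations), and Table 4 omits the item. Read literally, no. Steps 2 and 3 disagree.

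**4. What would adjustment do?** The plan gives no figure for the expectation gap or its effect on outcome, so there is nothing of the plan's own to reproduce on this point. The following is an illustration.

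Inputs:
- Total risk difference (RD) 0.16: the lower end of the 16 to 27 % in Sample size, read as a risk difference.
- Probability of improvement under advice about 0.50: assumed; the article gives none.
- Shift d in expectation caused by the active arm, 0.3 to 0.8 SD: assumed.
- Slope b, the gain in improvement probability per SD of expectation, 0.05 to 0.10: assumed.

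Model: E = d·T + noise with SD 1; P(improved) = 0.5 + (0.16 − d·b)·T + b·E. The total effect is (0.16 − d·b) + d·b = 0.16, of which d·b runs through expectation. With 2,000,000 simulated participants (one active arm against advice), the crude estimate was compared with the Mantel-Haenszel (MH) estimate over quartiles of E:

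MH RD = Σ[(a·n0 − c·n1)/n] / Σ[n1·n0/n]

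Here a and c are the numbers improved in the active and advice arms of a stratum, n1 and n0 the arm sizes, and n = n1 + n0.

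| d | b | d·b | Crude RD | MH RD | Share lost | Crude RR | MH RR |
|---|---|---|---|---|---|---|---|
| 0.3 | 0.05 | 0.015 | 0.160 | 0.147 | 8 % | 1.320 | 1.290 |
| 0.3 | 0.10 | 0.030 | 0.160 | 0.134 | 16 % | 1.320 | 1.262 |
| 0.5 | 0.08 | 0.040 | 0.160 | 0.126 | 21 % | 1.322 | 1.243 |
| 0.8 | 0.05 | 0.040 | 0.160 | 0.125 | 22 % | 1.319 | 1.242 |
| 0.8 | 0.10 | 0.080 | 0.159 | 0.089 | 44 % | 1.317 | 1.167 |

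Share lost = (crude RD − MH RD) / crude RD; for example (0.160 − 0.147)/0.160 = 8 % and (0.159 − 0.089)/0.159 = 44 %. The loss is slightly smaller than d·b because quartiles control E only coarsely.

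**5. Contrast with a true baseline covariate.** With d = 0 and b = 0.10, the RR is 1.32 both crude and stratified. Adjustment for a variable that allocation cannot change does not move the estimate.

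**6. Collider check under the null.** Set the effects of treatment and expectation on outcome to zero. Let an unmeasured U load 0.5 on expectation and add 0.10 per SD to the improvement probability. Exact conditioning on E gives a bias of −0.10 × 0.5 × d: −0.025 for d = 0.5 and −0.040 for d = 0.8. The quartile-stratified simulation gave RD −0.022 and −0.034, that is RR 0.96 and 0.93, against a crude RR of 1.00. Reversing the sign of one of U's effects reverses the bias.

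**7. Consequence for power.** With 600/4 = 150 per arm, two-sided 0.05 (assumed) and 50 % improved under advice, RD 0.16 gives about 80 % power. Putting 0.147 and 0.089 into the same formula gives about 73 % and 34 %. This is approximate, because it applies an unadjusted formula to an adjusted effect.

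**The case against.** The strongest reply is that the operative rule already excludes the variable. Statistical analyses speaks of baseline factors, and the article defines baseline data as complete before unmasking. The purpose clause in Limitations refers to expectations of recovery, which is the wording used for the item asked before allocation. Testing is not adjusting, and adjustment is conditional. Intention-to-treat comparisons by RR, RD and t-test are planned separately, and none is described as adjusted.

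Much of this stands. A reader might infer that the plan commits to adjusting the primary comparisons for a mediator, or that its screening rule is bound to select this variable. The document says neither, and it does not say that an adjusted estimate would replace the crude one. A reader might also expect the distortion to be largest against advice. No figure supports that: the advice arm has therapist contact, a booklet and up to three sessions, and the expectation gap is unknown.

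The reply does not remove the point. The plural in Limitations most naturally covers all three listed items, and the post-unmasking item is the only one that allocation can make differ systematically. Nothing excludes that item or labels its use as mediation or sensitivity analysis. The narrower wording in Statistical analyses is therefore one side of a contradiction.

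**Conclusion.** The point holds in limited form. The protocol article names a post-randomisation variable among the factors to be tested as confounders, and this conflicts with its own restriction to baseline factors. That the variable cannot confound the randomised comparison follows from its timing and needs no assumption. The harm is contingent: it arises only if testing leads to adjustment.

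Under the assumed shifts and slopes, about 8 to 44 % of a 0.16 risk difference would be lost. The loss would be a gain if the active arm lowered expectation, and collider bias could add to or offset it. A reader might infer that more than half of the effect would vanish. That can be constructed on a continuous scale: a total of 0.25 + 0.5 × 0.3 = 0.40 SD falls to 0.25 through mediation alone, and to 0.25 − 0.5 × (0.16/1.16) ≈ 0.18 if a shared cause loads 0.4 on both variables with unit residual variance. The last step rests on a freely chosen strength, so the document does not support that figure.

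The objection does not extend to previous experience or to Baseline B expectation of recovery.

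**What to change.** Amend the sentence in Limitations to agree with Statistical analyses: only variables recorded before the envelope is opened (among those listed, previous experience and Baseline B expectation of recovery) are candidates for adjustment.

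State that post-unmasking expectation stays out of the primary and any adjusted treatment-effect estimates. Report it descriptively by arm, which still informs readers about the lack of blinding. Use it beyond that only in an analysis labelled as exploratory mediation, with the assumption of no unmeasured common cause of expectation and outcome stated.

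The cost is wording only. The questionnaire, data collection and sample size are unchanged, and the article reports recruitment as still ongoing, so the change can precede analysis.

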## Trial status

The manuscript reports the protocol for an ongoing trial, for which patient recruitment is currently ongoing. The first study participant was included in September 2014 and by May 2015, 340 study participants had been included.

## Abbreviations

CPQ: Chronic Pain Questionnaire
NRS: Numerical rating scale
GEE: Generalized estimating equations
RR: Relative risk
RD: Risk differences
CI: Confidence intervals
